## Abstract

**Background:**

Cardiac rehabilitation programs aim to improve health status and to decrease the risk of further cardiac events. Persons undergoing rehabilitation often have difficulties transferring the learned health behaviors into their daily routine after returning home and maybe to work. This includes physical activity as well as fruit and vegetable consumption. Computer-based tailored interventions have been shown to be effective in increasing physical activity as well as fruit and vegetable consumption. The aim of this study is, to support people in transferring these two learned behavior changes and their antecedents into their daily life after cardiac rehabilitation.

**Methods:**

The study will have a randomized controlled design and will be conducted among German and Dutch people who participated in cardiac rehabilitation. The study will consist of one intervention group which will be compared to a waiting list control group. During the eight week duration of the intervention, participants will be invited to participate in the online after-care program once per week. The intervention encourages participants to define individual health behavior goals as well as action, and coping plans to reach these self-determined goals. The effectiveness of the program will be compared between the intervention condition and the control group in terms of behavior change, antecedents of behavior change (e.g., self-efficacy), ability to return to work and increased well-being. Further, subgroup-differences will be assessed including differences between the two countries, socioeconomic inequalities and across age groups.

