### Participants and recruitment

Participants will be recruited in cardiac rehabilitation facilities in Germany and the Netherlands*.* The study population will consist of people aged up to 85 years who successfully completed cardiac rehabilitation. In order to be eligible to participate in this study participants need to be able to use a computer, familiar with the use of the Internet, and need sufficient reading and writing language skills in the relevant language (German or Dutch). Patients with contraindications for physical activity and fruit and vegetable consumption will be excluded (e.g., heart failure patients which are not allowed to eat 2 pieces of fruit per day [5]).

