### Power analysis

The power analysis was based on the assumption that the intervention will result in a small improvement of effect to improve fruit and vegetable consumption and in a small to medium effect to improve physical activity for the study conditions [38]. The calculation was based on an effect size of 0.3, with a power (1-β) of 0.8 and alpha of 0.05.

No cluster effect is expected due to the fact that the randomization of the participants is independent of the place of recruitment. Further, it is necessary to take interaction effects into account between the intervention and the control group, and between Germany and the Netherlands.

Therefore, to be able to detect a small to medium effect, 263 people have to participate in every group in each country. This means that the required total sample size will need to consist of 1052 participants, not adjusted for potential drop out during the intervention.

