### Demographic and socioeconomic characteristics

Several items address the demographic and socioeconomic characteristics. These include gender, age, level of education, family status, living conditions, country of origin, native language and employment status.

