### Statistical analysis

Descriptive statistics will be used to describe baseline characteristics of the study. We will assess whether there are significant differences between the intervention group in comparison with the control group according to physical activity and nutrition by means of linear regression analysis in PASW (SPSS). The pre-test and post-test measurements of the control group will be compared with the measurements of the intervention and controle group with regard to the target behaviours.

To be able to assess the impact of the intervention on the performance of physical activity and fruit and vegetable consumption, we intend to perform several analyses of covariance (ANCOVA) after four weeks (T3) and six months (T4), controlling for the baseline performance. Multivariate regression analysis will be used to determine possible confounding or modification effects. Regression analysis will allow us to identify the percentage of variability of the dependent variable that is explained by the determinants used. In order to detect differences between the study condition and the control group, effect sizes will be calculated for each study group separately [78].

Subgroup analyses will be performed to determine if the benefit of the intervention depends between groups like nationality or socioeconomic status [79]. Further, dose–response-analyses will be conducted with logistic regression to see if the intervention effect depended on the time spent on the webpage.

Baseline characteristics of participants who dropped out will be compared with participants who finished the intervention to examine whether drop out is at random or determined by specific characteristics.

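### Testing effect modification by age across age groups gives up power that continuous age would keep, and no joint model of age, education and country is assured

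*Protocol article*

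**What the plan says.** Three places in the protocol article bear on effect modification.

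- Abstract, Methods: "subgroup-differences will be assessed including differences between the two countries, socioeconomic inequalities and across age groups". This is the only place where age groups are mentioned. No number of groups and no cut-points are given.
- Statistical analysis: "Subgroup analyses will be performed to determine if the benefit of the intervention depends between groups like nationality or socioeconomic status". Age is not named here, and the list is open. The same section plans ANCOVA at T3 and T4 adjusted for baseline performance, and a multivariate regression to look for possible confounding or modification. The terms of that regression are not listed.
- Main study outcomes: the programme effect is to be compared between countries as part of the primary parameter, while age and socioeconomic status are among the other parameters to be considered.

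The data for a finer analysis exist. Under Demographic and socioeconomic characteristics: "These include gender, age, level of education, family status, living conditions, country of origin, native language and employment status". Under Participants and recruitment, the population is "people aged up to 85 years who successfully completed cardiac rehabilitation", so the age range may be wide; no lower limit, mean or SD is stated.

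**The concern.** Two things are at stake.

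First, cutting a continuous modifier into groups throws away the variation within each group. If the effect rises or falls steadily with age, the test for modification loses power, and with several groups it also spends extra degrees of freedom. Cut-points that are not fixed in advance can also be chosen after the data are seen.

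Second, country is not randomised. The Background describes different routes into rehabilitation in Germany and the Netherlands, so the national samples may differ in age or education. If the effect depends on age, a country contrast that ignores age picks up part of that dependence. This matters because the Background presents the comparison between the two rehabilitation systems as the distinctive feature of the study.

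**Working it through.** **The plan's own figure.** Power analysis: "The calculation was based on an effect size of 0.3, with a power (1-β) of 0.8 and alpha of 0.05", with "263 people have to participate in every group in each country" and 1052 in total. 4 x 263 = 1052 is consistent. The 263 does not follow from the stated inputs: 2 x (1.960 + 0.842)^2 / 0.3^2 = 2 x 7.849 / 0.09 = 174.4, so 175 per arm two-sided; an arm x country interaction of 0.3 needs 4 x 7.849 / 0.09 = 348.8, so 349 per cell. That is a separate matter. Here 1052 is taken as given, without dropout, because the article states that it is "the required total sample size will need to consist of 1052 participants, not adjusted for potential drop out during the intervention".

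**Assumptions not in the documents.** Age distribution, size of the age modification, linearity, and the age difference between countries. Outcome SD is 1, allocation 1:1, alpha 0.05 two-sided.

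**Step 1: continuous age.** SE of the arm x age slope per SD of age = 2 / sqrt(1052) = 0.0617. The slope detectable with 80% power is 2.802 x 0.0617 = 0.173 SD of outcome per SD of age. With baseline adjustment at an assumed correlation of 0.5, the SE is 2 x sqrt(0.75) / sqrt(1052) = 0.0534, and a slope of 0.15 gives 0.15 / 0.0534 = 2.81, again 80%. Either way the non-centrality is about 7.85.

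**Step 2: age in equal-sized groups.** The share of information kept is the between-group share of the age variance: 2/pi = 0.637 for a median split of normal age, and 1 - 1/k^2 for k groups of uniform age. Omnibus power uses the non-central chi-square with k - 1 df. Trend power is Phi(sqrt(non-centrality) - 1.96).

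| Groups | Kept, normal age | Non-centrality | Omnibus power | Trend-score power | Kept, uniform age | Omnibus / trend power, uniform age |
|---|---|---|---|---|---|---|
| 2 | 64% | 5.00 | 61% | 61% | 75% | 68% / 68% |
| 3 | 79% | 6.23 | 60% | 70% | 89% | 65% / 75% |
| 4 | 86% | 6.75 | 57% | 74% | 94% | 61% / 77% |

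Continuous age gives 80% in every row. A median split of normal age would need 1052 x pi/2 = about 1653 participants to regain 80%.

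**Step 3: country contrast without age.** Suppose there is no true country modification, the age slope is 0.173, and mean age differs between countries by s SD. The expected spurious arm x country interaction is 0.173 x s. Its SE is about 4 / sqrt(1052) = 0.123 (0.124 in simulation). A simulation with 1000 replicates at 1052 participants gave:

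| Age difference s | Expected bias | Simulated bias | Falsely significant |
|---|---|---|---|
| 0 | 0 | about 0 | 5% |
| 0.25 SD | 0.043 | 0.05 | 7% |
| 0.5 SD | 0.087 | 0.09 | 12% |
| 1 SD | 0.173 | 0.17 | 29% |

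The normal approximation gives 6%, 11% and 29% for the last three rows, in line with the simulation. With age and arm x age in the model, simulated bias was about 0 and rejection 3-5%. At s = 0.5 the SE rose from 0.124 to 0.127.

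**The case against.** The strongest reply is that the article does not fix the weak method. Age groups appear once, in a one-sentence abstract summary. The Statistical analysis section does not name age as a subgroup and does plan a regression for confounding or modification, which is the right tool for separating country from age. Coding of covariates and the terms of an interaction model are commonly left to an analysis plan, which is not shown here. Much of this stands. It rules out calling the plan wrong or incomplete on this point.

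A reader might infer that each modifier is to be examined in its own subgroup analysis, and that the plan therefore cannot separate a country difference from an age or education difference. The text does not support that. Neither the abstract nor the Statistical analysis section says that the modifiers are taken singly, and the planned regression could hold them together. What can be said is only that a joint model is not assured, because no terms are named.

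The sizes are also open to challenge. They rest on assumed normality, linearity, slope and national age difference. A trend score recovers much of the loss, and a non-monotone age effect could favour groups. An age difference of 0.25 to 0.5 SD moves the false-positive rate for country only from 5% to 7-12%. Finally, age is listed among the other parameters and not among the main ones.

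What remains is that the only statement about how age will be examined points to groups, and a better test is available at almost no cost.

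**Conclusion.** The concern holds as a modest, inexpensive improvement. If modification by age is roughly linear and age is roughly normal, a slope that continuous age would detect with 80% power is detected with 57-61% power by an omnibus test over two to four groups, or 70-74% by a trend score over three or four. With uniform age the corresponding ranges are 61-68% and 75-77%.

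A country contrast taken alone would be biased by the age slope times the difference in mean age: about 0.09 SD for an assumed slope of 0.173 and a 0.5 SD difference. The documents give neither quantity, so this shows what could happen and does not predict it. Joint modelling removes the part due to measured modifiers only; country stays tied to its rehabilitation system.

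**What to change.** In the baseline-adjusted ANCOVA or regression already planned, state that modification by age is tested as an arm x age interaction with age in years as a continuous term. Check linearity, for example with a quadratic term and its interaction with arm. Fit arm x age, arm x country and arm x education in one model, so that each is adjusted for the others. Report the estimated programme effect with confidence intervals at a few ages fixed in advance, and use age groups for display only. Bring the abstract and the Statistical analysis section into line on which modifiers are examined.

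The cost is wording: all the variables are already collected and no participants are added. The downsides are a linearity assumption that has to be checked and a slightly wider interval for the country interaction when age and country are related. In the example above its SE goes from 0.124 to 0.127 at a 0.5 SD age difference, and to 0.138 at 1 SD.

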**Discussion:**

The present study will make a contribution to understanding how such an online-based tailored interventions enables study participants to adopt and maintain a healthy lifestyle. Implications can include how such an online program could enrich cardiac rehabilitation aftercare further.

**Trial registration:**

NTR 3706, NCT01909349

## Background

Cardiovascular diseases (CVDs) are a major health problem in western countries and cause approximately 30% of the global deaths [1,2] and 48% of the deaths in the EU [3]. Medical cardiac rehabilitation is a multifaceted approach to improve social, mental and physical recovery from any cardiac event. This rehabilitation aims at preventing future events by reducing CVD risk behaviors such as insufficient physical activity and unhealthy nutrition patterns [4]. Regular physical activity and healthy nutrition habits are important components within rehabilitation treatment [5], as these lifestyle changes reduce mortality and morbidity in CVD cases [6,7].

Physical activity has a wide range of beneficial effects and has been proven to be protective against several diseases such as hypertension, type 2 diabetes mellitus and obesity [8-10]. As a result of regular physical activity patients in rehabilitation gain a better physical condition, muscle strength and report a reduction of pain [11,12]. Studies also reveal that CVD patients have reduced mortality and morbidity if they improve their physical condition [13,14]. Furthermore, maintenance of physical activity is associated with a 45% risk reduction for subsequent CVDs [15].

The benefits of a diet rich in fruit and vegetables have been extensively studied and revealed that it reduces the risk of future cardiovascular issues and lowers CVD mortality by approximately 27% [16-20]. Furthermore, fruit and vegetable consumption reduces the risk factors for cardio vascular diseases like high cholesterol levels [21]. A healthy diet increases health (e.g., via a reduction of body weight) and is therefore important for people undergoing rehabilitation [22,23].

Even though several studies have demonstrated that adhering to rehabilitation treatment will reduce medical costs [24] and reduce morbidity and mortality by 20% to 25% [25], it is difficult for many patients in rehabilitation to adopt and especially maintain healthy behaviors after they participated in rehabilitation programs [26-28].

Because of these health benefits, the maintenance of a healthy lifestyle is important for those patients beyond the duration of the rehabilitation treatment. Yet, aftercare programs are limited and not always available for cardiac rehabilitation patients [29]. Computer-based tailored health interventions are a promising tool for multiple behavior change and provide several benefits: patients can take part in the aftercare from home and do not have to travel; patients can participate at their preferred time and it is cost-effective because more people can be reached compared to face-to-face or group aftercare programs [29-32]. Due to simplicity and ease of use online-based programs promise to be effective in implementing the new behavior changes into daily routines. Computer-based programs also provide the opportunity to deliver tailored messages. Tailored feedback is more effective than generic messages which provide standardized information [33,34] and also more cost effective [35,36]. Current studies have shown promising results in raising the motivation of patients in rehabilitation to increase fruit and vegetable consumption and physical activity [37,38]. However, these previous studies have not made use of computer based personalized feedback which might increase their effectiveness.

This personalized information is based on individual assessment, meets individual needs and contains less redundant information. Therefore personalized information is remembered better and increases the intention to change behavior [39-41]. Tailored messages should include different kinds of feedback: personal behavioral feedback and action feedback to increase the effectiveness [33]. Personal feedback provides the person with a reflection of the actual behavior [42]. This feedback mechanism increases the risk perception, awareness and the motivation to change [43,44]. Action feedback provides the individual with practical information about how to change and maintain certain behaviors [45]. Tailoring can be categorized into two broad forms: static and dynamic. Static tailoring is based on one assessment at the beginning of the intervention while dynamic tailoring can be done by assessing the information needed at the relevant time before the feedback is given. Dynamic tailoring was shown to be more effective in health behavior change interventions [34,41].

This research project will be conducted and evaluated in the Netherlands and Germany to investigate if an online-based rehabilitation aftercare program is equally effective in countries with different rehabilitation systems.

In the Netherlands, the majority of cardiac patients receive aftercare from their general practitioner (GP) after discharge from hospital. Only a small percentage of CVD patients (28%) receive rehabilitation [46]. Most of these patients receive rehabilitation in policlinics (80%), a minor part is treated in rehabilitation centers (20%) [5]. The Netherlands have a dense network of medical facilities working together (hospitals, policlinics, rehabilitation centers, medical practices) enabling patients to reach cardiac rehabilitation without long travel distances [47].

In Germany, the number of patients who receive cardiac rehabilitation is low as well. Only one third of cardiac patients are transferred to rehabilitative treatment [48]. However, in contrast to the Netherlands, rehabilitation in Germany mainly takes place as an inpatient service and patients are seldom able to stay at home during partaking the rehabilitation treatment [49,50]. This implies that, in contrast to the Netherlands, a major part of the patient education needs to be provided in the clinical setting. In the Netherlands the majority of persons undergoing rehabilitation is treated within policlinics for several hours a week and can stay in their home environment. Besides, the concept of aftercare in Germany differs from that in the Netherlands. In Germany, CVD patients are offered intensive aftercare rehab (IRENA), intensive after care (INA) and cardiac exercise groups with the aim of reintegration into the work life [48]. This aftercare is not provided in the Netherlands [51]. How these structural differences work together or boost the effect of an online intervention addressing health behavior adoption and maintenance was not tested before and is the main unique feature of this study.

### Study aims

The aim of the present study is to test the effectiveness of the online-based aftercare program “RENATA (Rehabilitation aftercare program for an optimal transfer into daily life)” for cardiac rehabilitation in order to improve physical activity and fruit and vegetable consumption. To acquire a deeper understanding of the usefulness of aftercare interventions in countries with different rehabilitation systems, the study will be implemented in Germany and the Netherlands.

## Methods

### Ethical approval

The study protocol was approved by the Medical Ethics Committee of Atrium Medical Centre Heerlen in the Netherlands (METC number 12-N-124) and by the *Deutsche Gesellschaft für Psychologie* (DGPs; EK-A-SL 022013). The study was registered with ClinicalTrials.gov (Identifier: NCT01909349).

### Study design

This multinational and multicenter longitudinal study has a quasi-experimental randomized controlled trial design. The study consists of one intervention group (IG) and one waiting list control group. The intervention group will first address physical activity then fruit and vegetable consumption. The waiting list control group will get access to the intervention after the study condition has finished the intervention (T3). The waiting list control group has to complete the baseline questionnaire (T1) at the same time as the intervention group and will have access to the intervention only after their second measurement. In total, six data collection time points are planned where T0 is intended for the collection of contact information only. Baseline measurement will take place at T1 before the intervention starts, followed by a measurement (T2) after completion of the intervention. Further follow-up measurements are planned to take place after four weeks (T3), after six months (T4) and after 12 months (T5) (see Table 1).

**Table 1 T1:** Design of measurement points

**Time point**	**Measurement**
T0	Patients within cardiac rehabilitation will be asked if they are interested in participation of an aftercare program. Contact data will be collected

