	**End of the intervention period**
	**Waiting list control group starts intervention**
T3	4 week follow-up measurement
T4	6 month follow-up measurement
T5	12 month follow-up measurements

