### Randomization

During the rehabilitation period, patients will be recruited within the rehabilitation center by their therapists. These therapists will first inform the person undergoing rehabilitation about the study and hand out study information. Participants will log in on the project website and have to give online informed consent. Randomization will be done by the computer software *TailorBuilder*, which is developed for internet based tailored interventions. Participants will be randomly allocated to the study group or to the waiting list control group. The waiting list control group will get access to the intervention after eight weeks (see Table 1).

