Table 2 presents a short overview about the weekly intervention content. During the first session, participants will receive feedback and information about their risk perception, outcome expectancies and their behavior with regard to physical activity and fruit and vegetable consumption which is based on the previous assessment. During the following session, participants formulate their own individual goals and specific plans with regard to physical activity and fruit and vegetable intake. Participants will receive information about how to structure a plan as good as possible. For example *“I would like to go for a walk in the park for 30 minutes each Tuesday.”* All plans have to be evaluated with regard to their feasibility through self-reflection. This will be achieved by asking the participants questions like: *“Is your plan ‘to go for a walk in the park’ easy to implement into your daily routine?*”

**Table 2 T2:** Intervention content

**Weekly sessions**	**Weekly content**
Session 1 PA and Session 5 F&V	Questionnaire and personalized feedback, increase risk perception and outcome expectations, defining own health outcomes; (Session 5: Assessment of social cognitive factors)
Session 2 PA and Session 6 F&V	Personalized feedback, defining action plans
Session 3 PA and Session 7 F&V	Personalized feedback
	Evaluation and self-reflection about action plans
	Adjusting action plans
	Defining personal barriers
	Develop personal coping plans
	Evaluation and refection about coping plans
Session 4 PA and Session 8 F&V	Personalized feedback, adjusting coping plans, thinking about social support and development of a list of potential supporters from the social environment; (Session 8: T2 questionnaire)

**(PA)** physical activity; **(F&V)** fruit and vegetable consumption.

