## Discussion

The results of this study are important for the future development of online-based rehabilitation aftercare programs for cardiovascular patients and the development of online interventions in general. Although there is no doubt about the positive effect of adequate physical activity and fruit and vegetable consumption for people undergoing rehabilitation [8,11,13,17,22,80], many patients fail to maintain lifestyle changes [26-28]. To transfer the rehabilitation results into the daily life and to overcome unhealthy habits, effective rehabilitation aftercare is necessary.

Given the benefit of tailored health behavior change interventions, there is still a need for further research. It is important to develop guidelines for interventions which are effective in different countries with different rehabilitation systems. In order to make a positive contribution, an international implementation and evaluation of this study will be done within Germany and the Netherlands.

It will be assessed to what extent the health status, quality of life and return to the labor market can be realized among the participants. Our hypothesis is that participants in the intervention group will increase their level of physical activity, fruit and vegetable consumption and are able to maintain these behaviors over a longer period of time compared to the control group.

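### Controls get access at T2 (week 8), not at T3 as labelled, so both named ANCOVAs (T3 and T4) compare against controls who already have the programme

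*Protocol article*

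**What the plan says.** The Study design section gives the time of control access twice. The first statement is "The waiting list control group will get access to the intervention after the study condition has finished the intervention (T3", where the bracket names T3. The next sentence says that controls "will have access to the intervention only after their second measurement". The same paragraph defines T2 by the words "followed by a measurement (T2) after completion of the intervention", and says that T0 collects contact details only.

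Table 1 places the end of the intervention at T2, after 8 weeks. It then has the row "Waiting list control group starts intervention", and only after that T3. The Randomization section says "The waiting list control group will get access to the intervention after eight weeks".

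For the analysis of impact on the two primary behaviours, the Statistical analysis section says "we intend to perform several analyses of covariance (ANCOVA) after four weeks (T3) and six months (T4), controlling for the baseline performance". It also mentions a linear regression between groups and a comparison of pre-test and post-test measurements, without a time point for either. The Discussion states the hypothesis that intervention participants improve both behaviours and "are able to maintain these behaviors over a longer period of time compared to the control group".

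**The concern.** A waiting-list design gives a comparison with untreated controls only until the controls are let in. The access point therefore decides which measurements can show the effect of the programme, and the protocol gives two different answers.

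If access is at T2, neither named ANCOVA is a comparison with untreated controls. At T3 the comparison would also mean different things for the two primary behaviours, because the programme treats physical activity first and fruit and vegetables second. At T4 both arms have been offered the whole programme. A null result there could mean that the programme does nothing, or that it works in both arms. A plan that reads the T4 result as the effect of the programme, or as evidence on maintenance against no programme, would report the wrong quantity.

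**Working it through.** **Step 1: where access falls.**

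| Source | Access point |
|---|---|
| Study design, bracketed label | T3 |
| Study design, next sentence | after the controls' second measurement: T0 is contact data, T1 the first, T2 the second |
| Study design, definition of T2 | T2 is the end of the intervention, the event that the disputed sentence labels T3 |
| Table 1 | between T2 and T3 |
| Randomization | after eight weeks, which is T2 in Table 1 |

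Four statements agree on T2, week 8. Only the label differs.

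**Step 2: the calendar, in weeks from T1.** T2 = 8. T3 = 8 + 4 = 12. The article does not say where the six months to T4 start, so T4 = 26 (counted from T1) or 8 + 26 = 34 (counted from T2).

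**Step 3: what controls have been offered.** There is one session per week. Table 2 assigns sessions 1 to 4 to physical activity and 5 to 8 to fruit and vegetables; the closing row of the two blocks is "Session 4 PA and Session 8 F&V".

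- At T3: 12 − 8 = 4 weeks of access, so 4 of 8 sessions. That is 4 of 4 for physical activity and 0 of 4 for fruit and vegetables.
- At T4: 26 − 8 = 18 or 34 − 8 = 26 weeks of access. The programme could be finished at week 8 + 8 = 16, which is 26 − 16 = 10 or 34 − 16 = 18 weeks before T4.
- If the T3 label were taken literally, access would start at week 12 and the programme could be finished at week 20. That is still 26 − 20 = 6 or 34 − 20 = 14 weeks before T4. The T3 comparison would then be clean, but T4 would not.

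**Step 4: illustration of the dilution.** The Power analysis section gives an effect size of 0.3, power 0.8, alpha 0.05 and 263 per group per country. A plain two-group comparison with those inputs (two-sided) needs 175 per arm, so it does not reproduce the 263. That is a separate matter, and 263 is taken here as the planned size.

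Let s be the share of the effect that controls gain. No figure for s is given, so the values below are assumptions. The contrast is d = 0.3 × (1 − s), and power is approximately Φ(d × √(n/2) − 1.96), two-sided, without baseline adjustment or drop-out. Example: s = 0.5 and n = 263 give d = 0.15 and 0.15 × √131.5 = 1.72, so Φ(−0.24) ≈ 0.40.

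| s | d | Power, 263 per group (one country) | Power, 526 per arm (both countries) |
|---|---|---|---|
| 0% | 0.30 | 93% | >99% |
| 25% | 0.225 | 73% | 95% |
| 50% | 0.15 | 40% | 68% |
| 75% | 0.075 | 14% | 23% |

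**The case against.** The strongest reply is that the comparison at T2 is already planned. The Statistical analysis section opens with a between-group regression and a pre-test/post-test comparison, and in this schedule post-test most naturally means T2, with T3 and T4 as follow-up. That may be the intention. But the text names no time point, states no baseline adjustment, and does not identify this comparison as the one with untreated controls. The analyses it does tie to the impact of the intervention are those at T3 and T4.

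A second reply is that the controls' second measurement might be T3. Table 2 places the T2 questionnaire inside session 8, which controls have not reached at week 8. This would fit the bracketed label and make the T3 ANCOVA clean. It cannot be squared with Table 1 or with the eight weeks in the Randomization section, and it leaves T4 affected. It does show that the protocol should say how controls complete T2.

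Three further points stand as limits:

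- Fruit and vegetable intake at T3 is largely unaffected on the week-8 reading. The split may not be perfect, because the Intervention section describes first-session feedback on both behaviours.
- The dilution shares are illustrative. The pooled comparison keeps 95% power if controls gain a quarter of the effect.
- Immediate versus delayed access is a legitimate contrast in a waiting-list trial, provided it is named as such.

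**Conclusion.** The concern holds. The T3 label is wrong against four other statements, and the access point is T2, week 8. Both named ANCOVAs fall after that point, and T4 does so on any reading of the protocol. T3 mixes a comparison with controls already offered the full physical activity block and one with controls offered essentially no fruit and vegetable sessions. The T4 ANCOVA estimates immediate versus delayed access, and cannot test the maintenance hypothesis if the control group is understood as untreated.

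The timing result rests only on the stated schedule and on controls being offered one session a week. The loss of power depends on the assumed share of the effect that controls gain. It ranges from nothing to a fall to 14% (one country) or 23% (both countries) over shares of 0% to 75%.

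**What to change.** 1. In Study design, change the bracketed T3 to T2, and give the same access point (T2, week 8 from T1) there, in Table 1 and in Randomization. State that controls complete the T2 questionnaire at week 8, outside session 8 and before access opens.
2. In Statistical analysis, add a baseline-adjusted ANCOVA at T2 for both behaviours, and name it as the comparison with untreated controls.
3. Report T3, T4 and T5 as immediate versus delayed access. Note that at T3 controls on schedule have been offered only the physical activity sessions.
4. Reword the maintenance hypothesis in the Discussion to match.

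The cost is wording. No new measurement point is needed, because the protocol already makes control access wait for their second measurement, which on the schedule is T2. The downside is that the effect against untreated controls is shown only at the end of the intervention. Maintenance against untreated controls cannot be shown with this design.
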